### Design

Figure 2 shows an overview of the TELESCOPE study design. We are conducting a cluster RCT with primary care clinicians as the unit of randomization into either (1) the TELESCOPE intervention arm, or (2) an EUC arm. Patients of clinicians in the TELESCOPE arm receive the decision coaching intervention delivered by trained patient navigators (hereafter referred to as ‘decision coaching session’) prior to an upcoming clinic visit with their primary care clinician. Patients of clinicians in the EUC arm have the opportunity to participate in an LCS discussion with their primary care clinician at an upcoming clinic visit. Usual care is enhanced by providing clinicians in both the TELESCOPE and EUC arms with access to a Continuing Medical Education (CME) webinar about LCS and an LCS discussion guide. Patients in the TELESCOPE arm who complete initial screening with negative or benign findings are due for their next screening in 12 months. Half of these participants are randomized to receive a telehealth decision coaching booster session with a patient navigator 1 month before their next annual screening. Table 1 provides a summary of components for the TELESCOPE and EUC arms, which are described in greater detail below.

For the TELESCOPE Trial, a community advisory board of diverse community stakeholders reviews and guides intervention development, recruitment strategies, study procedures, patient-facing materials (e.g., study flyers, informed consent forms, surveys, intervention materials), implementation (e.g., patient recruitment, retention, cultural acceptability), interpretation and dissemination of the results, and identification of next steps.

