After the decision coaching session, the patient navigator alerts the nurse navigator to place an order for an LDCT for LCS, typically within 1 week of the patient indicating she/he wants to be screened. The LDCT order is reviewed and signed by the patient’s primary care clinician, typically within 24–48 hours. Nurse navigators follow up with the clinician if the order is not signed during this time period. Study staff reach out to imaging centers within 48 hours of the LDCT order being signed by the clinician to check if the LDCT order has been received and if they have contacted the patient about scheduling. Patients receive a follow-up call from a patient navigator if they have not scheduled their screening within 2 weeks, and a re-navigation call from a patient navigator if they have not completed screening within 3 months.

For TELESCOPE arm patients randomized to receive the decision coaching booster session, patient navigators follow the same process as the initial decision coaching session and a similar script to the Decision Coaching Manual. At the end of the booster session, patients are asked whether they want to pursue screening, and if the answer is yes, similar procedures as abovementioned are followed.

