### Patient Electronic Health Record (EHR) Reviews

A key secondary outcome is initial LCS uptake within 6 months after the decision coaching session (TELESCOPE) or the scheduled clinic visit date (EUC). Other secondary outcomes include adherence to annual LCS among those with an initial low-risk LDCT result by 18 months after the decision coaching session, tobacco treatment referral, receipt of tobacco treatment, and clinical outcomes, including diagnostic testing, cancer diagnoses, and treatment. For the TELESCOPE arm participants, data abstractions are conducted after the initial decision coaching session at 3 months (to trigger re-navigation for those who have not completed screening despite expressing a preference for it), 6 months (to assess initial LCS uptake, tobacco treatment referral/receipt, and clinical outcomes), 12 months (to assess follow-up testing in patients with Lung-RADS^®^ score of 3 or 4, tobacco treatment referral/receipt, and clinical outcomes^51^), and 18 months (to assess adherence to annual LCS, tobacco treatment referral/receipt, and clinical outcomes). For the EUC arm participants, data abstractions are conducted at 6, 12, and 18 months after their initial scheduled clinic visit for the same outcomes.

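### Annual screening adherence is read at a fixed 18 months from coaching or visit, so the time left after the repeat scan falls due shrinks from 6 months to 0 as the first scan moves from month 0 to month 6

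*Protocol article*

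**What the plan says.** Four statements in the protocol article fix the timing.

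- **First scan.** Under Patient Electronic Health Record (EHR) Reviews: "A key secondary outcome is initial LCS uptake within 6 months after the decision coaching session (TELESCOPE"), or after the scheduled clinic visit in EUC.
- **Due date of the repeat.** Under Design, TELESCOPE patients who "complete initial screening with negative or benign findings are due for their next screening in 12 months".
- **Read-out.** Under EHR Reviews, the outcome is "adherence to annual LCS among those with an initial low-risk LDCT result by 18 months after the decision coaching session". The same section places the abstraction that reads it at "18 months (to assess adherence to annual LCS, tobacco treatment referral/receipt, and clinical outcomes"). Footnote b of Table 2 starts the 18-month clock at the coaching session for TELESCOPE and at the scheduled visit for EUC.
- **Steps that affect when scans happen.** Under TELESCOPE Intervention, the order is typically placed within a week and signed within 24–48 hours. There is a call at 2 weeks if nothing is scheduled, and "a re-navigation call from a patient navigator if they have not completed screening within 3 months". EHR Reviews adds a TELESCOPE-only abstraction at "3 months (to trigger re-navigation for those who have not completed screening despite expressing a preference for it"). Half of the TELESCOPE patients with a low-risk first scan are randomised to a booster one month before the repeat is due.

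The article states no allowance around the due date. It does not say whether a repeat done before the 12-month date counts, or how patients with little time left are handled.

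**The concern.** The due date runs from the first scan, but the read-out runs from coaching or the visit. How long a patient can be observed after the repeat falls due is therefore set by when the first scan happened. That is a post-randomisation event, and the intervention is designed to change it. A raw percentage at month 18 mixes patients with almost six months to return and patients with almost none.

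Annual adherence is named in Aim 1b, and the Discussion gives better annual adherence as the reason for the booster. Unequal observation time lowers the adherence percentage overall. It can also create or hide a difference between arms if first-scan dates are distributed differently in the two arms.

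**Working it through.** **Inputs from the article:** first-scan window 0–6 months (EHR Reviews); interval to the repeat 12 months (Design); cut-off 18 months from coaching or visit (EHR Reviews; Table 2, footnote b); booster 1 month before the due date (Design; Table 1); re-navigation at 3 months, TELESCOPE only (TELESCOPE Intervention).

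**The plan's own figure.** 6 + 12 = 18. The cut-off equals the latest due date for a patient counted in initial uptake, with no margin.

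**Time left.** For a first scan at month t, the repeat is due at t + 12. Time left is 18 − (t + 12) = 6 − t. The booster falls at t + 11, so booster to cut-off is 18 − (t + 11) = 7 − t.

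| First scan (month) | Repeat due (month) | Left after due date (months) | Booster to cut-off (months) |
|---|---|---|---|
| 1 | 13 | 5 | 6 |
| 2 | 14 | 4 | 5 |
| 3 | 15 | 3 | 4 |
| 4 | 16 | 2 | 3 |
| 5 | 17 | 1 | 2 |
| 6 | 18 | 0 | 1 |

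If first scans were spread evenly within each half of the window (an assumption), the mean time left would be 4.5 months for months 0–3 and 1.5 months for months 3–6.

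**Illustration of the under-count.** The article gives no return times. Assume that every patient returns, with an exponential delay after the due date of median m months, and that first scans are spread evenly within each period. With λ = ln 2 / m, the share captured by month 18 is

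- first scan in months 3–6: 1 − (1 − e^(−3λ)) / (3λ)
- first scan in months 0–3: 1 − (e^(−3λ) − e^(−6λ)) / (3λ)

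| Median delay m (months) | First scan months 0–3 | First scan months 3–6 |
|---|---|---|
| 0.5 | about 100% | 76% |
| 1 | 95% | 58% |
| 2 | 78% | 38% |
| 3 | 64% | 28% |

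**What this could do between arms.** Suppose that the share of late (months 3–6) first scans differed by 20 percentage points between arms while true return behaviour was identical. The spurious difference in adherence would be 0.20 × (1.00 − 0.76) = 4.8 points at m = 0.5, 0.20 × (0.95 − 0.58) = 7.4 at m = 1, 0.20 × (0.78 − 0.38) = 8.0 at m = 2 and 0.20 × (0.64 − 0.28) = 7.2 at m = 3. It would count against whichever arm had more late first scans. The 20-point gap is an assumption; the article gives no first-scan timing for either arm.

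**The case against.** The best defence is that 18 months is simply the uptake window plus one screening interval. That makes it a tight choice rather than a contradiction, and a full protocol or analysis plan may define adherence more closely. The first part is fair. The second does not remove the point, because the article itself fixes both the cut-off and its starting point, and that starting point does not match the due date.

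Three stronger readings are tempting, and the documents do not support them.

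- *Re-navigated TELESCOPE patients are non-adherent by construction.* A reader might infer this from the 3-month re-navigation step. But first scans at months 3, 4 and 5 still leave 3, 2 and 1 months. Only a first scan at about month 6 or later leaves nothing, and then only if a repeat done before the due date is not credited, which the article does not say.
- *The bias runs against TELESCOPE.* Re-navigation can add late first scans there. The rapid order, the signature follow-up, the imaging-centre check and the 2-week call pull first scans forward in the same arm. EUC patients face the same 6 − t limit from their visit. The net direction cannot be read from the article.
- *The booster effect is cut off.* Booster and no-booster patients are randomised within TELESCOPE, so the short window is balanced in expectation. The order, signature and 2-week call normally fall before or around the due date. If the 3-month call is repeated after the booster, it falls at t + 14, beyond month 18 when t > 4; but that is a back-up step, not one that every patient needs. The consequence is dilution.

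**Conclusion.** The point holds as a mismatch between the clock and the due date. Time at risk for annual adherence falls from 6 months to 0 as the first scan moves from month 0 to month 6. That follows from the article's own figures with no further assumption, provided that the repeat is expected at or after its due date. Late first screeners in either arm are under-counted.

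The size of the under-count depends on return times that the article does not give. In the illustration, 28–76% of returning patients first screened in months 3–6 are captured, against 64–100% of those screened in months 0–3. Bias between arms is possible, with its direction unknown. In the booster comparison the loss is a lower adherence rate and a diluted effect, not a tilt towards one group.

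This affects one secondary outcome in the screened low-risk subset. It merits correction because the outcome belongs to a stated aim and the remedy is cheap.

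**What to change.** **Preferred.** Define annual adherence from each patient's own initial LDCT date. Replace the raw 18-month percentage with an analysis of time from initial to repeat LDCT, administratively censored at the 18-month abstraction and still adjusted for clustering by clinician. It needs the two scan dates from the records already being abstracted, so the cost is a little more analysis work. Two limits should be stated. Censoring comes 18 − t months after the first scan, so the month of first scan should enter as a covariate or stratum in case late screeners also return later. A patient first scanned at month 6 contributes nothing after the due date.

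**Alternative.** Use one common window after the initial LDCT for everyone, with a length chosen by the investigators, and extend the last abstraction to cover it. With an allowance of g months after the due date, follow-up must reach 18 + g months for a month-6 first scan; for example, g = 3 needs month 21. The cost is one later abstraction in the screened low-risk subset. At the planning rates, 210 × 25.5% + 210 × 14% ≈ 54 + 29 = 83 patients would be screened by month 6; the article does not give the low-risk share of these.

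Under either option, state whether a repeat before the 12-month date counts and whether a first scan after month 6 enters the denominator. Recruitment began in May 2023 and the article appeared in April 2024, so no patient had reached month 18 at publication.

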### Implementation Outcomes and Data Collection

The implementation potential of the TELESCOPE trial is evaluated based on PRISM constructs. ^33^
Table 3 summarizes the data source and measures for each PRISM construct. Surveys are conducted at baseline (T0) for all clinicians, practice administrators, and navigators, and at 12 months (T1) after the first enrolled patient visit for clinicians and navigators. Semi-structured interviews are conducted at T1 for selected clinicians, practice administrators (i.e., medical directors of each site), and navigators. The surveys assess characteristics of organizational recipients and their acceptability of the intervention. The semi-structured interviews assess their perspectives on the intervention, implementation and sustainability infrastructure, and the external environment to identify barriers or facilitators to implementation of the intervention.

### Health Professional Surveys

Clinicians. The T0 clinician survey collects their demographic data, current practices related to LCS, perceptions about organizational readiness for change (ORIC) ^52^, and beliefs about LCS (adapted from LCS-12^39^). The T1 clinician survey evaluates their beliefs about LCS and perceptions about the acceptability of the SDM and counseling visit (using the Acceptability of the Intervention Measure (AIM), Intervention Appropriateness Measure (IAM), and Feasibility of Intervention Measure (FIM) ^53^).

Navigators. The T0 navigator survey collects their demographic data, perceptions about ORIC, and knowledge of LCS (LCS-12^39^). The T1 navigator survey assesses their perceptions about the acceptability of the SDM and counseling visit with the AIM, IAM, FIM measures^53^.

Practice Administrators. The T0 practice administrator survey collects their demographic data and site-level characteristics such as the number of clinicians in their practice, patient volume, and information about clinical workflows related to LCS.

### Health Professional Semi-Structured Interviews

Semi-structured interviews will be conducted with TELESCOPE arm clinicians and navigators (12 months after the initial decision coaching session), EUC arm clinicians (12 months after first EUC patient enrollment), and practice administrators (12 months after the first patient enrollment at their site). To ensure representation of a variety of practice settings and patient populations, clinicians and practice administrators are randomly selected for the interview and are stratified based on the following criteria: internal medicine versus family medicine, academic versus non-academic sites, and RWJBH versus UH sites. We will oversample for clinicians from sites that serve large numbers of Black and Hispanic patients. All navigators involved in the study will be invited to participate in interviews. The semi-structured interview guide is developed based on the PRISM constructs. ^33^ Interviews will take approximately 45 minutes and be audio-recorded.

### Intervention Efficacy and Reach

To assess intervention efficacy, we track the proportion of patients obtaining LCS and tobacco treatment in each study arm. To assess reach of the TELESCOPE intervention, we track the proportion of patients who completed the decision coaching session with the patient navigator among patients consented and randomized to the TELESCOPE arm.

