### Aims

The trial’s aims are to: (1) test the effectiveness of a decision coaching intervention for LCS delivered by patient navigators (TELESCOPE) versus EUC (enhanced usual care delivered by their primary care provider) on: a) quality of the SDM process about LCS (primary outcome); b) initial LCS uptake and subsequent adherence to annual LCS; and c) tobacco treatment referrals and receipt of tobacco treatment for current smokers; d) assess potential mediators and moderators of intervention effects; and (2) evaluate the implementation potential of patient navigator-delivered decision coaching for LCS by identifying organizational-, clinician-, and patient-level factors that might be barriers or facilitators to successful implementation.

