### Conceptual Framework

This trial uses an effectiveness-implementation hybrid type I design and is guided by the Practical, Robust Implementation and Sustainability Model (PRISM) as the implementation framework. ^32,33^ PRISM accounts for the role of organizational and patient perspectives, external environment, implementation and sustainability infrastructure, and recipient characteristics in the success of an intervention. ^33^ The impact of the intervention will be evaluated using the constructs in the RE-AIM (reach, efficacy, adoption, implementation, and maintenance) framework, which is a component of PRISM. ^33^ The TELESCOPE intervention uses the implementation strategy of ‘revising professional roles’ by training patient navigators to lead the SDM discussion because clinicians often lack the time and training to provide high quality SDM during clinic visits. ^34^

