### Patient Recruitment and Enrollment

Using the Epic electronic health record (EHR), study staff identify patients who have an upcoming non-acute clinic appointment with a participating clinician in the next 2 months and who are potentially eligible for the study based on their age and smoking history. Subsequently, participating clinicians are emailed a list of their patients who are potentially eligible and asked to identify and notify study staff within 1 week if any patients on the list should not be contacted to participate in the study. Study staff then send approved potential patient participants a study invitation email containing a link to the pre-screening eligibility form. We also developed a 1-page recruitment flyer with culturally relevant images of patients, key eligibility criteria for the study, study activities, benefits of participating in the study, and study team contact information. The recruitment flyer is sent out to potential patient participants by email (if their email addresses are available), regular mail, and via the Epic patient portal (if their portal is activated). Subsequently, study staff reach out via telephone to potential patient participants to introduce the TELESCOPE study, answer questions, assess interest in participating, determine LCS eligibility, and consent eligible patients who are willing to participate. We employ evidence-based practices for enhancing recruitment and retention including incentives, an interculturally competent recruitment flyer, study specific community advisory board, persistence, skilled teamwork, and an interculturally competent staff. ^35–37^

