### Trial Status

Recruitment started in May 2023. As of early April 2024, 117 clinicians were participating in the trial and 134 patient participants have enrolled in the study. Recruitment of participants is expected to be completed by May 2026.

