a The decision coaching materials include: (1) a 2-page LCS Discussion Guide with a summary of the benefits and harms of LCS and questions guiding patients in making a shared decision on LCS with their clinician; (2) a Decision Coaching Manual, which includes a script for the patient navigator to use during the decision coaching session; (3) Decision Coaching Slides which are used by the patient navigator during the session and serve as a visual aid for patients; and (4) Frequently Asked Questions (FAQs) to help patient navigators answer patients’ questions.

**Table 2 T2:** Patient-Reported Measures and Timepoints.

Construct/Measures	No. of Items	Baseline Survey (T0)	1-Week Survey (T1)^a^	6-Month EHR Review^b^	12-Month EHR Review^b^	18-Month EHR Review^b^
Sociodemographics, Health Literacy, Medical History^65,66^	19	X				
Quality of SDM Process^47^	4		X			
Knowledge of LCS^39^	12	X	X			
Decisional Conflict^40^	10	X	X			
Preparation for Decision Making (PrepDM) ^48^	10		X			
LCS Discussion with Clinician	1		X			
Cancer Fatalism^41^	3	X				
Social Norms^42^	6	X				
Medical Mistrust^43^	7	X				
Perceived Racial Discrimination in Healthcare^44,45^	2	X				
LCS Health Beliefs^46^	35	X	X			
Intention to Undergo LCS	2	X	X			
Telehealth Patient Satisfaction^49^	6		X			
Ottawa Acceptability measure^50^	10		X			
Initial LCS Uptake	-			X		
Follow-Up on Lung-RADS 3 or 4 cases	-				X	
Adherence to Annual LCS	-					X
Tobacco Treatment Referral	-			X	X	X
Receipt of Tobacco Treatment	-			X	X	X
Cancer Diagnoses and Treatment	-			X	X	X

a The T1 survey is administered 1-week after the scheduled clinic visit for both TELESCOPE and EUC arm patients.

b The 6-, 12-, and 18-month data abstractions are from the initial decision coaching session for TELESCOPE arm patients and from the scheduled clinic visit for EUC arm patients.

**Table 3 T3:** Implementation Measures based on Practical, Robust Implementation and Sustainability Model (PRISM) Constructs.

PRISM Construct Assessed	Data Source and Timing	Measure(s)
Reach	Ongoing Electronic Health Record (EHR) review	Proportion of patients who completed the decision coaching session with the patient navigator among patients consented and randomized to the TELESCOPE arm

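### Reach is defined only among consented TELESCOPE-arm patients, so it is a coaching-completion rate and cannot show what share of potentially eligible patients was reached

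*Protocol article*

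**What the plan says.** Under Intervention Efficacy and Reach, reach is the "proportion of patients who completed the decision coaching session with the patient navigator among patients consented and randomized to the TELESCOPE arm". The Reach row of Table 3 has the same numerator and denominator, with ongoing EHR review as the data source. The article gives no other reach measure.

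Two sections give the measure its role. Conceptual Framework states: "The impact of the intervention will be evaluated using the constructs in the RE-AIM (reach, efficacy, adoption, implementation, and maintenance) framework". Implementation Outcomes and Data Collection states: "The implementation potential of the TELESCOPE trial is evaluated based on PRISM constructs", and refers to Table 3, where Reach is the first row.

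Patient Recruitment and Enrollment describes what happens before a patient can be counted. Staff search the EHR on age and smoking history for patients with an upcoming non-acute visit. Then "participating clinicians are emailed a list of their patients who are potentially eligible", and clinicians may name patients who should not be contacted. Staff approach the rest by email, post, portal and telephone, check eligibility, and consent those who are eligible and willing.

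**The concern.** A reach figure is normally read as saying how far a programme gets into the population it is meant for. Here the people it fails to get to are removed before the denominator is formed: those never contacted, those who decline, and eligible patients whom the clinician holds back. What remains is whether volunteers, having agreed to a study of lung screening, attend the session.

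At stake is the interpretation of one named implementation measure. The Background presents identification of potentially eligible patients in primary care as a way to include minority populations, and the Discussion stresses diverse practices. If losses between the EHR list and the coaching session differ by race, ethnicity or practice type, this measure will not show it.

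A minor point of wording: the definition speaks of patients randomized to the arm, but the Design section makes clinicians the unit of randomization. The denominator is in effect the consented patients of TELESCOPE clinicians.

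**Working it through.** The article states no expected value of reach, so there is no figure to reproduce. The check is whether the defined ratio can carry information about eligible patients.

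**Inputs**
- Planned TELESCOPE-arm enrolment: 210 patients (Sample Size and Power Calculation).
- Completion of coaching among enrolled patients: not given; assumed 80%, 90% or 100%.
- Share of eligible patients of TELESCOPE clinicians who consent: not given; assumed 10% to 100%.

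**Identity**

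completed / eligible = (completed / consented) × (consented / eligible)

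The protocol's reach is the first factor alone. The second factor does not enter it.

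**Numbers put in.** With 210 enrolled, the number eligible is 210 / consent share. The number coached is 210 × completion, that is 168, 189 or 210.

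| Consent share (assumed) | Eligible patients | 80% complete (168) | 90% complete (189) | 100% complete (210) |
|---|---|---|---|---|
| 10% | 2100 | 8% | 9% | 10% |
| 20% | 1050 | 16% | 18% | 20% |
| 30% | 700 | 24% | 27% | 30% |
| 50% | 420 | 40% | 45% | 50% |
| 100% | 210 | 80% | 90% | 100% |
| **Reach as the protocol defines it, every row** | | **80%** | **90%** | **100%** |

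For example, 189/210 = 90% is reported in every row of the 90% column, while coverage of eligible patients is 189/2100 = 9% in the first row and 189/210 = 90% in the last. (The 189 and 420 here are products of the assumed shares. That they match the article's post-attrition arm size and total sample is coincidence.)

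**Reading.** Within each column the protocol's figure is constant while coverage of eligible patients varies tenfold. The two agree only if every eligible patient consents. The ratio is therefore a completion rate and does not identify the share of eligible patients reached.

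**The case against.** The strongest defence is that the denominator is stated openly and identically in both places, and the article never presents the ratio as population coverage. Completion among enrolled patients is itself useful for feasibility. No threshold or decision rule depends on it. All of this stands, and it limits the point to what the measure is called and what should be reported beside it.

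The article also commits to CONSORT reporting for cluster trials and refers to a patient flow figure that is not shown, so some of the recruitment counts may be published anyway. This stands in part: flow counts would supply the raw numbers, but nothing in the text links them to the reach measure.

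A wider denominator has its own weaknesses. The EHR lists screen only on age and smoking history, so eligibility stays unknown for patients never contacted. Patient Eligibility Criteria excludes patients whose clinician deems them unable to undergo screening or treatment, so some held-back patients are properly ineligible and not missed. The numerator is bounded by the enrolment target, and refusing a trial is not refusing a programme. These objections stand and shape the fix, but they do not turn the present ratio into a measure of coverage.

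A reader might also infer that the measure fails a question posed by Aim 2. The document does not support that. Aim 2 is to "evaluate the implementation potential of patient navigator-delivered decision coaching for LCS by identifying organizational-, clinician-, and patient-level factors" that act as barriers or facilitators; it asks for no share of eligible patients. Reach bears on implementation potential only through the PRISM and RE-AIM constructs.

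**Conclusion.** The point holds as a matter of definition: reach is fixed, in two places, as coaching completion among enrolled patients, and it cannot show what share of potentially eligible patients was reached. It is a cheap improvement to one descriptive implementation measure. The primary outcome, the effectiveness comparisons and the sample size are unaffected.

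The size is not known. The 9% to 90% range for a reported 90% rests wholly on the assumed completion and consent shares.

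Two stronger readings are not supported:
- A reader might quote a multiple by which reach is overstated. Any such multiple is just 1 / consent share, and the article gives no consent share. Nor does it offer the ratio as coverage, so there is no stated coverage figure to be overstated.
- Trial Status reports that "117 clinicians were participating in the trial and 134 patient participants have enrolled in the study", and 134 / 117 = 1.15 patients per clinician might look like evidence of low consent. It is not, because the numbers listed and contacted are not given and the count covers both arms. Recruitment runs from May 2023 to May 2026, about 36 months, and some 11 had passed. Pro rata that is 420 × 11/36 = 128 patients, so 134 is about on pace.

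**What to change.** 1. Under Intervention Efficacy and Reach and in Table 3, rename the present ratio 'coaching completion among enrolled patients', with the denominator worded as consented patients of TELESCOPE-arm clinicians.
2. Add reach as sessions completed divided by potentially eligible patients of TELESCOPE clinicians on the EHR lists actually worked. Exclude those found ineligible, including those the clinician deems unable to undergo screening or treatment. Restricting to worked lists keeps the figure from depending on when enrolment stops.
3. Report aggregate counts of patients held back by the clinician, not contacted, declined, consented and coached, by practice type and by race and ethnicity where recorded. Tie these counts to the CONSORT flow diagram.
4. State the limits beside the figure: eligibility is unknown for uncontacted patients, and trial refusal is not programme refusal, so this is a trial-based approximation to reach in routine care.

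The cost is wording plus tabulation of lists that staff already make, provided the steps are logged by arm. That should be confirmed while recruitment is still open. The new figure can be no higher than the present ratio and will probably be lower.
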